# Synopsis

**Title**  Efficacy, safety and tolerability of Atorvastatin 40 mg

in patients with relapsing-remitting multiple sclerosis treated with interferon-beta-1b - Follow up study

**SW**iss **A**torvastatin and Interferon-**B**eta 1b Trial **I**n **M**ultiple **S**clerosis **Follow up-study**

**Short title “SWABIMS Follow up-study”**

**Study phase**  Phase IIb study

**Study design** Multi-center, randomized, rater-blinded, parallel-group-study in Switzerland

**Investigational product, dosage,** Atorvastatin 40 mg every day (oral) plus Interferon-beta

**route of administration** 1b 250g given subcutaneously (s.c.) every other day (e.o.d)

**Reference product, dosage,** Interferon-beta-1b 250g given

**route of administration** subcutaneously (s.c.) every other day (e.o.d)

###### Indication Relapsing-remitting multiple sclerosis (RR-MS)

**Study objectives** Comparison of efficacy, safety and tolerability of combination of Atorvastatin 40 mg (per os) daily and Interferon-beta-1b e.o.d in patients with relapsing-remitting or secondary progressiveforms of multiple sclerosis compared to monotherapy with Interferon-beta-1b e.o.d over a period of **12 months after successful finishing the SWABIMS-study**.

**Primary Endpoint** Efficacy of Atorvastatin as add-on therapy to a basic treatment with Interferon-beta-1b measured by the proportion of patients with new T2 lesions after 12 months of treatment.

**Secondary Endpoints** Gd-enhancing lesions on T1-weighted images after 12 months of treatment.

Total T2-hyperintense lesion volume (burden of disease, BOD) after 12 months of treatment.

Cortical atrophy (changes in brain volume, changes in grey matter and white matter) on MRI after 12 months of treatment

Clinical disease progression (EDSS, MSFC)

Functional systems scores (of EDSS and MSFC)

Number of relapse-free patients after 12 months of treatment

Relapse rate after 12 months of treatment

Time to first relapse

Sieric levels of anti-MOG- and anti-MBP-antibodies

Sieric levels of NAb

**Patient population** Men and womenwith relapsing-remitting forms of Multiple Sclerosis (according to McDonald’s criteria), **that have successful finished the SWABIMS-study**.

**Study design and Methodology** Multi-center, rater-blinded, parallel-group, two arm, randomized study.

**Safety** Physical examination, registration of adverse events and laboratory analysis will be performed at scheduled visits and, if adverse events are spontaneously reported, also at unscheduled visits.

**Duration of treatment**  12 months

**Number of study centers** 8

**Total number of patients** Approx. 60

**Adverse events** As interviewed or reported spontaneously by the patients or as noted on physical or laboratory examinations

**Planned start and end date** April 2007 – April 2009

**of recruitment**

**Manufacturer(s) of the** Schering AG: Interferon-beta-1b (Betaferon)

**investigational /** Pfizer AG: Atorvastatin (Sortis)

# Investigators and study administrative structures

## Investigators

For each study center, the following roles are to be identified:

- Treating physician
- Evaluating physician
- MRI investigator

In addition, further support staff may be identified.

# Introduction

**Multiple Sclerosis** (MS) is the most common neurological disorder causing disability in young adults affecting approximately 1 in 1000 persons in western countries (1). The clinical manifestations usually begin at the age of 20 to 40 years with a median age of onset of 28 years with acute episodes of neurological dysfunction, followed by periods of partial or complete remission and clinical stability in between relapses (2). This relapsing-remitting phase (RR-MS) of the disease is usually followed by progressive clinical disability (secondary progressive phase, SP-MS). Sometimes, relapses and partial remissions are superimposed on the chronic progression (3; 4). In a minority of patients, the disease progresses from the onset and does not remit (primary progressive, PP-MS).

Multiple sclerosis is considered to be a chronic inflammatory demyelinating autoimmune disease of the central nervous system, which involves T-cell-mediated immune reactions destructing myelin sheaths and axons (26). The prevention of autoimmunity requires mechanisms to actively silence or tolerize self reactive T cells in the periphery. For example, expansion of CD25+CD4+ T regulatory cells, which constitute 5 - 10 % of peripheral CD4+ T cells in humans, prevents autoimmunity by suppressing the activation of self-reactive T cells (27). It has been observed that professional antigen presenting dendritic cells (DC) may prime those CD25+CD4+ T regulatory cells to acquire suppressive properties (28). In MS this mechanism of tolerance may malfunction.

At present, there is no cure for multiple sclerosis and the management of MS-patients requires treatment with disease-modifying agents such as interferon-beta or immunsuppressants such as mitoxantrone, azathioprine or methotrexate. Acute relapses are usually treated with corticosteroids.

**Interferon-beta-1b** (Betaseron, Betaferon) is a non-glycosylated recombinant human interferon-beta approved for high-frequency, subcutaneous (sc) administration in the treatment of multiple sclerosis. In a randomised, double-blind trial in patients with relapsing-remitting MS (RRMS), interferon-beta-1b 250 micro g (8 million International Units [MIU]) every other day reduced the annual relapse rate and increased the proportion of relapse-free patients compared to placebo. It also reduced relapse severity, hospitalisations, and disease activity assessed by magnetic resonance imaging (MRI), and lengthened the time to a next relapse (5). The effect of interferon-beta-1b as seen on MRI in relapsing remitting multiple sclerosis was an approximately two-third reduction of disease activity (6). Beta-Interferon has been shown to exert multiple modulatory effects on immune cells, e.g. change of cytokine expression patterns, suppression of matrix metalloproteinase 9 (MMP) and others (30).

**Statins**are lipid-lowering drugs which inhibit the 3-hydroxy-3-methylglutaryl-coenzyme A (HMG-CoA-) reductase, which is the main regulatory enzyme of cholesterol biosynthesis. They lower cardiovascular-related morbidity and mortality and have a favourable safety profile being in clinical use for almost two decades (7). Side effects include hepatotoxicity (<3%) and myopathy (0.1-0.5%) (8). Rhabdomyolysis is the most severe form of muscle damage associated with statin use, although it is rare (9). The tolerability and the safety of Atorvastatin treatment, in line with other statins, are well documented by several trials, also at high doses, presenting a good risk-benefit curve (22, 23). In recent years many studies have demonstrated, that statins have anti-inflammatory and immunomodulatory properties in addition to their lipid-lowering effects. Therefore, statins seem to have therapeutic potential in immune-mediated disorders such as multiple sclerosis (10, 14, 29).

In ***experimental allergic encephalomyelitis (EAE)***, the animal model for the human demyelinating disease multiple sclerosis, oral statins attenuate the severity of disease progression by preventing or reversing chronic or relapsing paralysis. Statin-treated animals show delayed onset of the first clinical signs and milder clinical signs (11, 12, 24).

Lovastatin blocks the infiltration of mononuclear cells into the central nervous system (CNS), blocks the expression of extracellular adhesion molecule Leukocyte function antigen-1 (LFA-1) on leucocytes, inhibits the induction of proinflammatory cytokines and blocks the loss of myelin as a result of inflammatory disease in the CNS of EAE rats (12, 15).

Atorvastatin modulates the clinical course of murine experimental autoimmune encephalitis (EAE) in preventing or reversing chronic or relapsing paralysis as well. It induces signal transducer and activator of transcription (STAT) 6-phosphorylation and secretion of anti-inflammatory Th2-cytokines (IL-4, IL-5, IL 10), transforms growth factor (TGF)-beta and conversely inhibits STAT4-phosphorylation and secretion of inflammatory Th1-cytokines (IFN-, IL-2, IL-12, TNF-a) (11, 13, 14). Furthermore atorvastatin promotes the differentiation of Th0 cells into Th2-cells and reduces the CNS infiltration. It acts as direct inhibitor of induction of MHC class II expression by IFN- and thus as repressor of MHC-class II mediated T-cell activation. This effect is due to inhibition of the inducible promoter IV of the class II transactivator (CIITA) and is observed in several cell-types, including primary human endothelial cells and monocyte-macrophages (14). In addition adoptive transfer of atorvastatin-treated CD4+T cells prevents induction of EAE in recipient mice, which implies that statin-treatment induces a population of regulatory T cells which can suppress clinical autoimmune disease (11). Atorvastatin has pleiotropic immunomodulatory effects and may be beneficial by activating the pathway of tolerance.

Statins may also have neuroprotective properties. They upregulate endothelial nitric oxide synthase (eNOS) and inhibit inducible nitric oxide synthase (iNOS), effects which are both potentially neuroprotective. Moreover, eccito-toxicity caused by overstimulation of glutamate receptors is a major cause of neuronal death after a brain insult (18, 19, 20, 21, 24). Ex vivo, statins in combination with IFN beta-1b show synergistic effects in inhibiting the proliferation of stimulated peripheral blood mononuclear cells (PBMC) in a dose-dependent manner. Furthermore, statins reduced the expression of activation-induced adhesion molecules on T cells, reduces MMP-9 and downregulate chemokine receptors on both B and T cells (16).

In an open-label, single-arm study in ***patients with relapsing-remitting multiple sclerosis*** on use of oral simvastatin (80 mg), the mean number and volume of gadolinium-enhancing lesions compared to pretreatment brain MRI scans declined by 44% and 41% respectively, while treatment was well tolerated (17). In a very small study lovastatin therapy showed beneficial effects on the expanded disability status scale (EDSS), relapse rate and Gd-enhancing lesions (25).

**Multiple sclerosis patients** respond variably to monotherapies, which could be explained by different subtypes of multiple sclerosis and multiple environmental and genetic factors. Oral statins decrease neuroinflammatory activity and clinical signs in experimental allergic encephalomyelitis and showed beneficial effect in smaller studies in multiple sclerosis patients. Therefore, statins may have favourable clinical effects in patients with relapsing-remitting disease as single therapy, or administrated as combination therapy with interferon beta. To determine the therapeutic effect of statins in multiple sclerosis, further investigations of statins as therapeutic agents for MS should be addressed in larger controlled clinical trials and longer observation periods.

In this study the effect of Atorvastatin as add-on therapy in patients with RR-MS, already treated with interferon-beta-1b vs. treatment with Interferon-beta-1b alone will be evaluated over another 12 months after finishing the SWABIMS Study as a Follow up study of the SWABIMS-Study. The treatment of each patient will be the same. Furthermore important safety and tolerability data will be generated.

# Study Objectives

The objectives of this study are to assess the efficacy, safety and tolerability of the combination of Atorvastatin 40mg p.o. daily and Interferon-beta-1b sc e.o.d compared to monotherapy with Interferon-beta-1b sc e.o.d in patients with relapsing-remitting multiple sclerosis **for another 12 months after successful finishing the SWABIMS-Study**.

## Primary endpoint

The primary endpoint of the study is to determine the efficacy of Atorvastatin as add-on therapy to a basic treatment with Interferon-beta-1b, evaluating the disease activity measured by the proportion of patients with new T2 lesions after 12 months of treatment.

## Secondary endpoints

- Gd-enhancing lesion on T1-weighted images after 12 months of treatment
- Change of total T2 hyperintense lesion volume after 12 months of treatment (burden of disease, BOD)
- Clinical disease progression (EDSS, MSFC)
- Functional system scores (of EDSS and MSFC)
- Number of relapse-free patients after 12 months of treatment
- Relapse rate after 12 months of treatment
- Time to first relapse
- Cortical atrophy (changes in brain volume, changes in grey matter and white matter) after 12 months of treatment
- Sieric levels of antibodies against myelin oligodendrocyte glycoprotein (anti-MOG) and against myelin basic protein (anti-MBP)
- Sierial levels of neutralizing Antibodies (Nab)

# Study Design

- Multi-center, rater-blinded, parallel-group, two arms, randomized study. Patients with relapsing-remitting forms of MS, **who have successfully finished the SWABIMS-Study**, respecting all inclusion/exclusion criteria, will be treated with the same medication they have received during the SWABIMS-Study for another 12 months directly after finishing the **SWABIMS-Study**.
- In the **SWABIMS-study**, 80 patients with relapsing-remitting MS were randomized to either an Interferon-beta-1b-monotherapy (subcutaneous every other day) **or** to a treatment with Interferon-beta-1b (subcutaneous every other day) plus Atorvastatin 40mg/d for 12 months after they were treated with Interferon-beta-1b (subcutaneous every other day) for 3 months.
- Enrolment of approx. 60 patients (one half in the Atorvastatin group) is planned.
- Patients providing written informed consent will be ***treated for 12 months***.

## Selection of study population

### Inclusion criteria

- **Patients, who have successfully finished the SWABIMS-Study.**
- Patients with relapsing-remitting forms of multiple sclerosis (according to McDonald’s criteria)
- Patients must agree to avoid macrolids, including erythromycin and clarithromycin for the whole study duration
- Availability and willingness to continue study visits and procedures through month 12, even if discontinuation of study drug is necessary
- A woman of child-bearing potential must agree to avoid pregnancy with appropriate means while on study. Hormonal contraceptives used for more than 3 months are acceptable if therapy remains constant throughout the study
- Written informed consent
- Adequate bone marrow, renal, and hepatic function as defined in appendix.

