### Exclusion criteria

- Patients, who didn’t successfully finish the SWABIMS Study.
- Any disease other than multiple sclerosis that would better explain the patient’s signs and symptoms
- Primary progressive MS
- Uncontrolled, clinically significant heart diseases, such as arrhythmias, angina, or uncompensated congestive heart failure.
- Uncontrolled seizure disorder
- Myopathy or clinically significant liver disease
- Medical or psychiatric conditions that compromise the ability to give informed consent, to comply with the protocol, or to complete the study
- Inability, in the opinion of the principal investigator or staff, to comply with protocol requirements for the duration of the study
- Known hypersensitivity to either Atorvastatin or Interferon-beta or other human proteins including albumin
- Known hypersensitivity to gadolinium
- Inability to undergo a MRI scan
- A history of drug abuse in the 6 months prior to enter the study
- Patients will not be permitted to take any antilipidemic medications (refer to list below). Most other medications taken for treatment of chronic conditions is permitted, as well as most medications to treat minor treatment-emergent illness(es). Given the importance of Atorvastatin metabolism by cytochrome P450 3A4, only concomitant medications permitted in the package insert will be allowed during study participation. Consistent with the package insert, the following medications are expressly prohibited throughout the study:
- All lipid-lowering medications, including niacin, fibrates (e.g., clofibrate, fenofibrate, bezafibrate, gemfibrozil), bile acid sequestrants (e.g., cholestyramine, colestipol), and HMG-CoA reductase inhibitors (e.g. fluvastatin, pravastatin, simvastatin)
- Orlistat
- Macrolide antibiotics (e.g., erythromycin, azithromycin, clarithromycin)
- Azole antifungals (e.g., fluconazole, clotrimazole, itraconazole)
- Immunosuppressive medications (e.g., cyclosporine)
- Protease inhibitors
- Nefazodone
- Fish oils
- Grapefruit juice
- Previous (before start of study) therapy with any of the following: Monoclonal antibodies, mitoxantrone, cytotoxic or immunosuppressive therapy (excluding systemic steroids and adrenocoticotropic hormone; ACTH), total lymphoid irradiation.
- Participation in any other studies (**except the SWABIMS-Study**) involving investigational or marketed products, concomitantly or within 30 days prior to entry in the study

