### Removal of patients from the study

- Every patient or his/her legal representative has the right to refuse further participation in the study at any time and without providing reasons. A patient's participation is to terminate immediately upon his/her request. The investigator should seek to obtain the reason.
- The patient may be withdrawn from the study at any time at the investigator’s discretion; the reason should be documented.
- Patients who withdraw from the study will not be replaced.
- There are two different types of patient **withdrawals** that may be decided:
  1. Withdrawal from further **study participation**; *i.e*. study treatment will be discontinued and no further data will be collected for the patient withdrawn. For this type of withdrawal, before withdrawal all efforts should be made to perform all assessments scheduled for the end-of-study visit (except MRI).
  2. Withdrawal from further **study medication** without termination of study participation.

If premature termination of study medication is decided for a patient, all efforts should be made to keep that patient on the original visit schedule until the regular end-of-study visit *(i.e.*, irrespective of study medication, each randomized patient should be followed up for the originally scheduled duration).

For both types of withdrawal, the following general rules apply: as far as possible, any withdrawal of a patient should be decided only after consultation with the sponsor.

The reasons for any withdrawal are to be fully documented on the case report form (CRF).

- **Withdrawal criteria**

A patient must be withdrawn from further **study participation** under the following circumstances:

1. Withdrawal of consent: every patient has the right to refuse further participation in the study at any time and without providing reasons.
2. Participation in any other clinical trial during the duration of this study.

A patient must be withdrawn from further **study medication** under the following circumstances:

1. Non-attendance of visits

Study medication must be withdrawn if a patient does not attend two consecutive scheduled visits without a major reason agreed on by the sponsor.

1. Unauthorized use of study drug.
2. Pregnancy
   Patients who have been withdrawn from study drug treatment because of pregnancy should not undergo MRI scans while pregnant.
3. Psychiatric conditions

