### Treatment groups

#### Group 1 (Atorvastatin)

SWABIMS Study: After a treatment period of three months with Interferon-beta-1b 250 micro g (8 million International Units [MIU]) subcutaneously every other day, oral Atorvastatin (40 mg/d) was administered in addition for 12 months.

**SWABIMS Follow up Study:** The treatment withInterferon-beta-1b (subcutaneous every other day) and oral Atorvastatin (40mg/d) will be continued immediately after the end of the SWABIMS Study for 12 month.

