#### Pregnancy Test in Women

Serum beta-HCG

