### Procedures at baseline:

- Demographic data
- Inclusion and exclusion criteria
- Medical and surgical history
- MS history
- Medication history
- The contraceptive method used will be recorded, and if applicable, the age at menopause. Patients of childbearing potential will be instructed to discontinue study medication if they become pregnant and immediately notify the treating physician.
- Informed consent signature
- Vital signs
- Neurological examination by Evaluating Physician: EDSS
- MSFC scoring by Evaluating Physician or study nurse
- Physical examination
- Laboratory evaluations (Serum Chemistry, Serum lipids, Hematology, Urinalysis, Creatine phosphokinase, Thyroid Profile, Immunology (2 serum-probes stocks): Neutralizing Antibodies (Nab), Anti-MOG-, anti-MBP-Antibodies
- Pregnancy Test in women
- ECG
- MRI scan

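### Serum beta-HCG is scheduled at baseline, but no entry criterion uses the result and nothing requires it before the entry gadolinium MRI

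*Protocol*

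**What the plan says.** **Testing.** Section 8.2.2 lists "Serum beta-HCG" among the laboratory measurements. Section 10.1.1 includes "Pregnancy Test in women" among the baseline procedures. Table 1 shows the test at baseline and at no other visit. None of these places attaches an action to the result.

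**Entry.** Section 7.1.1 requires: "A woman of child-bearing potential must agree to avoid pregnancy with appropriate means while on study". Section 7.1.2 does not list pregnancy; its nearest item is "Inability to undergo a MRI scan". Section 7 makes treatment conditional on eligibility: patients "respecting all inclusion/exclusion criteria, will be treated with the same medication they have received during the SWABIMS-Study".

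**Pregnancy after entry.** Section 7.1.3 makes pregnancy a mandatory reason to stop study medication. It adds: "Patients who have been withdrawn from study drug treatment because of pregnancy" "should not undergo MRI scans while pregnant". Sections 8.3.4 and 10.1.1 have patients told to stop the medication and report a pregnancy.

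**The entry scan.** Section 8.4 requires an MRI of every patient at study entry, within 14 days of the visit. Section 15.1.3 specifies gadobutrol at 0.2 mmol/kg. Section 15.1.1 says that the screening scan doubles as the baseline scan, and section 10.1 identifies the screening visit with the parent study's month 15 visit.

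**The concern.** A pregnancy test exists to find a pregnancy that nobody yet knows about. It protects against a contrast scan only if the result is read first and something follows from it. Here the test is planned and the scan is mandatory, but the two are not linked.

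At stake is one contrast-enhanced scan of a woman whose pregnancy is unrecognised, in a protocol that elsewhere advises against MRI in pregnancy. A second, smaller gap is that no entry rule says what a positive result means for eligibility. This is a matter of participant and fetal safety, not of estimation or testing.

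**Working it through.** No arithmetic applies. The check is whether any provision makes the result a condition of entry or of the scan.

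**1. Does an entry criterion use the result?**
- Section 7.1.1 has seven inclusion criteria. One mentions pregnancy, as an undertaking about conduct during the study. A woman unaware that she is pregnant can give that undertaking honestly.
- The last inclusion criterion refers laboratory eligibility to the appendix. Section 15.2 gives ten limits: haemoglobin, white cells, neutrophils, platelets, lymphocytes, ALAT, bilirubin, creatinine, CPK and TSH. HCG is not among them.
- Section 7.1.2 names neither pregnancy nor a positive test.

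Result: no criterion excludes current pregnancy or requires a negative test.

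**2. Does anything put the result before the entry scan?**
- Section 8.4 gives a 14-day window around the visit and no order relative to the blood draw.
- Section 10.1.1 lists the pregnancy test ahead of the MRI. That list is not a reliable sequence: it puts the consent signature seventh, after demographics and the histories, while section 12.2 requires consent before selection procedures.
- Section 15.1.2 opens with a general check that the patient can be scanned and does not mention pregnancy. Section 15.1.3 moves to the contrast injection with no reference to a test.
- The condition in section 7 governs treatment. It does not mention the scan.
- The MRI sentence in section 7.1.3 is worded for patients already withdrawn from drug because of pregnancy. It cannot act before the pregnancy is known.

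Result: no sentence in the available text requires the result first.

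**3. Which safeguards reach which patient?**

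| Safeguard | Known pregnancy | Unrecognised pregnancy |
|---|---|---|
| Undertaking to avoid pregnancy (7.1.1) | probably | no |
| MRI ability and compliance exclusions (7.1.2) | probably | no |
| Instruction to stop and notify (8.3.4, 10.1.1) | yes | no |
| General pre-scan check (15.1.2) | probably | no |
| Mandatory drug stop and MRI advice (7.1.3) | yes | no |
| Serum beta-HCG, read before the scan | yes | yes |

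Only the last row covers an unrecognised pregnancy, and the protocol leaves open whether it is read before the scan.

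**4. What happens after a positive result?** The pregnancy is then known and section 7.1.3 stops study medication. The patient was already taking the same drugs in the parent study, so only doses taken while the result is pending could be added.

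**The case against.** **The other safeguards already cover it.** They probably do for a known pregnancy, and a positive result makes a pregnancy known. A reader might infer that the protocol would admit a woman known to be pregnant and keep her on treatment. The documents do not support that, because 7.1.3 requires the drug to be stopped. For known pregnancy, an explicit exclusion would be mainly clearer wording. The order of test and scan is the part that these safeguards leave open.

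**The scan may belong to the parent study.** Section 10.1 makes screening the parent's month 15 visit, section 10.2 starts treatment at that visit, and section 15.1.1 uses the screening scan as baseline. It may well be the parent study's own closing scan, done under that study's rules. A reader might infer that this protocol adds a contrast exposure; the text does not establish that. This objection stands as a limit on the point. It does not remove it, because this protocol lists both the test and the scan as its own baseline procedures and refers to no parent check.

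**Section 15.1.1 does not prove that the scan precedes eligibility.** It says the scan serves to check MRI inclusion criteria, but section 7.1 has no MRI criterion beyond ability to be scanned. This is fair: the phrase is weak evidence of order. The point rests on the absence of a stated order, not on this phrase.

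**Sites would read the test first anyway.** Many would, and the window allows it. The protocol does not ask them to.

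**The month 12 scan is more exposed.** That scan is clearly governed by this protocol and has no scheduled pregnancy test at all. This is correct, and the fix below does not cover it.

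**Conclusion.** The point holds as a minor participant-safety improvement. Followed exactly, the schedule permits a contrast scan of a woman with an unrecognised pregnancy before her already planned test is read, contrary to the position taken in 7.1.3.

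**Size.** Very few patients. Enrolment is about 60 men and women, and the number of women of child-bearing potential is not given, so no rate can be stated. Added drug exposure is negligible. The primary analysis is unaffected.

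**What it rests on.** The conclusion is about the protocol text available. The parent protocol is not shown and may already require a test before the month 15 scan. The patient information in section 16 is also not available and could carry instructions on pregnancy or MRI.

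**What it does not say.** A reader might infer that the entry criteria ignore pregnancy altogether. They do not: 7.1.1 addresses it, but only as something to avoid during the study.

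**What to change.** - In 7.1.2, add the exclusion: pregnancy (positive baseline serum beta-HCG).
- In 8.4 and 10.1.1, state that women of child-bearing potential need a negative result before the entry contrast MRI and before follow-up study medication is dispensed.

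The cost is protocol wording only, since the test is already scheduled. In practice the blood is drawn slightly earlier, or the scan waits briefly for the result within the 14-day window.

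These changes govern the entry scan only. The month 12 scan would still have no scheduled pregnancy test.
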